## Background

The prevalence of obesity is increasing worldwide. It has become an epidemic and is associated with many chronic diseases [1,2]. Although exercise is commonly cited as an important strategy for weight reduction, researchers in numerous well-controlled and statistically well-powered studies have demonstrated that exercise training without a dietary intervention results in far less weight loss than expected, given the expended calories. This is most evident when the exercise dose is substantial (≥60 min/day) [3]. In studies of regimens lasting 26 weeks or more (n = 12), researchers determined that there was no dose–response relationship between prescribed energy expenditure and weight loss and that actual weight loss was only 30% of what was expected [3].

The potential explanations for the failure of exercise training to produce the expected weight loss in long-term studies include poor exercise regimen adherence, reduced spontaneous activity, reduced resting metabolic rate and/or increase in energy (that is, food) intake. The results of well-controlled studies do not suggest that poor adherence is the source of the discrepancy between actual and expected weight loss. For example, Donnelly *et al*. examined the role of supervised exercise in weight loss over the course of 16 months in college-aged men and women [4]. The required exercise energy expenditure was 3,300 kcal/wk for men and 2,200 kcal/wk for women. Only the men lost weight (mean = −5.2 kg) compared to their control group peers, but the mean 5.2-kg weight loss was only 19% of what was expected (64 weeks × 3,300 kcal/wk)/7,700 kcal/kg = 27.4 kg), given the dose of exercise. Exercising women maintained their weight, despite expending 2,200 kcal/wk during exercise, and the nonexercising female controls gained weight. On the basis of these results, the researchers suggested that increased energy intake, rather than decreases in resting metabolic rate or spontaneous physical activity, might have contributed to the less-than-expected weight loss [4-6].

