After being screened into the trial, participants will complete the comprehensive baseline assessment and will be randomly assigned to one of the exercise arms (8 KKW or 20 KKW) or to the control group (nonexercise arm). Participants will be enrolled at a 2:1 female/male ratio and randomized separately to one of the three intervention groups at a 1:1:1 ratio to obtain an equal number of women and men in each treatment group. Participants who drop out (that is, fail to return for the 6-month examination) will not be replaced. Participants in the 8-KKW and 20-KKW intervention groups will continue to attend exercise sessions during week 4 and week 24 assessment periods. Participants who have not met the intervention energy expenditure goals by week 24 will be allowed to exercise up to 3 weeks after the week 24 assessment period.

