#### Difference between expected weight loss and observed weight loss

Observed weight loss will be calculated based on the difference in body weight from baseline to follow-up. Expected weight loss will be calculated using two methods. The first method assumes that 1 kg of weight represents 7,700 kcal of energy. Calories expended during supervised exercise is divided by 7,700 kcal to derive expected weight loss (exercise energy expenditure divided by 7,700 kcal/kg) [33]. The second method is based upon more recent research which demonstrates that a 7,700-kcal deficit does not always produce a 1 kg of weight loss, because this formula overestimates weight loss [34-36]. The researchers who produced this body of work developed a more accurate model that accounts for the dynamics of weight change during exercise. This dynamic formula will be used to calculate expected weight loss, given the two different doses of exercise, and the accompanying observed weight loss. Weight loss difference will then calculated as observed weight loss minus expected weight loss [33].

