Second, we will characterize compensators vs. noncompensators, where *compensators* will be defined as those who fail to lose the expected amount of weight during the exercise trial and *noncompensators* will be defined as those who meet or exceed the expected amount of weight loss during the trial. Differences between the groups on the following variables will be tested: (1) baseline values derived from self-report instruments, (2) baseline energy intake measures (for example, total kilocalories, macronutrient intake and fat and sugar intake) and (3) baseline activity levels (quantified by SenseWear armband readings). In addition, differences between compensators and noncompensators will be evaluated for sex and race disparities, and compensators and noncompensators will be compared with respect to changes in outcomes from baseline to week 24.

As an initial step in a mediator analysis, we will test whether changes in energy intake mediate or partially mediate the relationship between group assignment (exercise dose) and Wt Loss_diff_. We will follow the methods of Baron and Kenny [59] and determine whether Wt Loss_diff_ is predicted by group, with grouping variables coded as 8 KKW vs. 20 KKW and control vs. 20 KKW. Subsequently, we will test whether change in energy intake predicts Wt Loss_diff_. Assuming that the results are significant, we will then determine whether group significantly predicts Wt Loss_diff_ independently of energy intake. If group does not independently predict Wt Loss_diff_, then the relationship between group and Wt Loss_diff_ may be attributable to change in energy intake. That is, we will then conclude that change in energy intake mediated the relationship between group and Wt Loss_diff_. If the relationship between group and Wt Loss_diff_ is reduced after accounting for change in energy intake, then partial mediation will have been demonstrated.

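### Compensator status is judged on raw weight change from baseline, with no allowance for control-arm weight change, so background drift in either direction enters the label (secondary objective 3 only)

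*Protocol article*

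**What the plan says.** The article builds the label in two steps.

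- **Ingredients** (Difference between expected weight loss and observed weight loss). The observed side is fixed first: "Observed weight loss will be calculated based on the difference in body weight from baseline to follow-up". For the first method, "Calories expended during supervised exercise is divided by 7,700 kcal to derive expected weight loss". For the second, "This dynamic formula will be used to calculate expected weight loss, given the two different doses of exercise". Neither method is described as having a term for weight change without exercise.
- **Label** (Data analysis). Compensators are "those who fail to lose the expected amount of weight during the exercise trial"; noncompensators are "those who meet or exceed the expected amount of weight loss during the trial". The abstract and the secondary objectives define them in the same way.

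The control arm is used at group level: in the control versus 20-KKW contrast on Wt Loss_diff and in the group coding of the mediation analysis. It has no stated role in the individual label.

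On weight change without exercise, the Background says of one cited earlier trial: "Exercising women maintained their weight, despite expending 2,200 kcal/wk during exercise, and the nonexercising female controls gained weight". On sex mix, the assessment section says: "Participants will be enrolled at a 2:1 female/male ratio".

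**The concern.** Exercise energy divided by 7,700 kcal/kg predicts how much lighter a person will be than the same person would have been without exercising. Comparing that figure with change from baseline assumes that the second weight equals the baseline weight. If non-exercisers drift upward, an exerciser who responds exactly as predicted falls short of the cut and is called a compensator. If they drift downward, an exerciser who does compensate can pass it.

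Secondary objective 3 rests on this label. So do the comparisons in the Data analysis section: baseline questionnaires, intake and activity, sex and race, and change in outcomes to week 24. Drift that differs by sex would give a sex difference in compensation with no sex difference in the response to exercise. Drift in intake unrelated to exercise would raise both weight and measured intake change, and could be read as the mechanism of exercise compensation. The trial randomises a concurrent arm that estimates average drift, but the label does not use it.

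**Working it through.** **1. The plan's own figure.** The label has no stated operating characteristics. The nearest figure is the Table 3 power for Wt Loss_diff: difference 2.0 kg, SD 3.3 kg, 60 per arm, two-sided 0.05. By the normal approximation, (2.0/3.3) × √(60/2) = 3.32, and Φ(3.32 − 1.96) = 0.91, against 0.90 stated. This reproduces, so 3.3 kg serves below as the SD of an individual's observed minus expected loss.

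**2. Expected loss by the 7,700 rule over 24 weeks.**

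- 8 KKW, about 900 kcal/wk (abstract): 900 × 24 / 7,700 = 2.8 kg.
- 20 KKW, about 2,250 kcal/wk, which implies 2,250/20 = 112.5 kg body weight. With the ramp of 8, 14, then 20 KKW for 22 weeks: 112.5 × (8 + 14 + 440) / 7,700 = 6.75 kg.

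**3. Where the cut falls.** The Background puts actual loss at 30% of expected in studies of 26 weeks or more. Carrying that over to this trial is an assumption. The mean shortfall is then 0.7 × 2.8 = 1.96 kg at 8 KKW and 0.7 × 6.75 = 4.73 kg at 20 KKW.

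**4. Effect of drift.** Let g be the background gain (negative for a loss), assumed common to all, with normally distributed differences. The noncompensator share is Φ(−shortfall/3.3) on raw change and Φ(−(shortfall − g)/3.3) net of drift. The difference between the two is the share mislabelled.

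| Arm | Raw noncompensators | g = 0.5 kg: net; moved | g = 1.0 kg: net; moved |
|---|---|---|---|
| 8 KKW | Φ(−0.595) = 27.6% | Φ(−0.444) = 32.9%; 5.3 points | Φ(−0.292) = 38.5%; 10.9 points |
| 20 KKW | Φ(−1.432) = 7.6% | Φ(−1.280) = 10.0%; 2.4 points | Φ(−1.129) = 13.0%; 5.3 points |

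Because noncompensators are few, the share of net noncompensators who lose that label is larger: 16 to 28% at 8 KKW and 24 to 41% at 20 KKW.

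**5. Range.**

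- If the cut is central (mean observed loss equal to expected), the shift is Φ(0.5/3.3) − 0.5 = 6.0 points to Φ(1.0/3.3) − 0.5 = 11.9 points in either arm.
- At g = 0 nothing moves.
- A background loss of 0.5 to 1.0 kg moves 4.8 to 9.1 points at 8 KKW and 1.9 to 3.5 points at 20 KKW the other way: compensators are called noncompensators.

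**6. Distortion by dose.** An assumed 1 kg gain is 1/2.8 = 36% of expected loss at 8 KKW and 1/6.75 = 15% at 20 KKW.

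**7. Precision of a control correction.** The SE of the control mean change is 3.3/√60 = 0.43 kg pooled. With 40 women and 20 men (2:1 of 60) it is 3.3/√40 = 0.52 kg and 3.3/√20 = 0.74 kg. The sex difference in drift has SE √(0.52² + 0.74²) = 0.90 kg. These use the Wt Loss_diff SD for control weight change.

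**The case against.** **The evidence for drift is thin.** A reader might infer that the article reports background weight gain in women as something to expect in this trial. It does not. The statement that "the nonexercising female controls gained weight" concerns a cited 16-month trial in college-aged adults and gives no amount. This trial runs 24 weeks in overweight or obese adults aged 18 to 65, and its controls receive regular health information. Drift could be a gain, nil or a loss. This stands, and the sizes above are assumptions.

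**A 6 to 12% error is not the general figure.** It needs a central cut, which contradicts the article's own premise that exercise yields far less loss than expected. This also stands: at 20 KKW the figure is less than half of that.

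**A sex-specific correction could do harm.** The sex difference in control drift has an SE of about 0.9 kg, about as large as the bias it would remove or larger. It could create a sex gap as easily as remove one. This is a good reason not to make it the main definition.

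**The primary inference is protected.** Arm contrasts cancel drift common to the arms, and the primary objectives do not use the label. True; it limits the point to secondary objective 3.

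**It is a choice of construct.** The article defines compensation consistently as failing to lose the expected weight, and nothing contradicts it. As a description the raw label is legitimate. But the trial wants to explain a response to exercise, and for that reading drift has to be separated out. The objection supports keeping the raw label, not reporting it alone.

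**Conclusion.** The point holds in a limited form. The individual label compares raw change from baseline with a loss defined relative to not exercising, and no control-arm term appears. Average background drift is therefore counted as compensation or as its absence, and a sex difference in drift would appear as a sex difference in compensation.

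The likely size is modest in absolute terms: about 5 to 11% of exercisers at 8 KKW and 2 to 5% at 20 KKW. This rests on four assumptions: a common gain of 0.5 to 1.0 kg, observed loss at 30% of expected, normality with SD 3.3 kg, and expected loss from the 7,700 rule. Values under the dynamic formula are not shown and cannot be checked. The documents support neither a definite direction of bias nor any doubt about the primary Wt Loss_diff contrasts. The change is still worth making, because it is cheap and could alter the phenotyping conclusion.

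**What to change.** In the Data analysis section, keep the raw label and prespecify a control-adjusted classification beside it: each exerciser's observed change minus the pooled control-arm mean change, compared with expected loss. Carry the error of the control mean (about 0.4 kg) through by bootstrap. State that compensator characteristics and the sex comparison will be interpreted as responses to exercise only if they hold under both classifications. Use a sex-specific control correction only as a further sensitivity analysis, given its SE of about 0.9 kg for the sex difference.

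The cost is a little more analysis on data already collected, plus added noise from the control mean. The adjustment removes average drift only; individual drift and noise around the cut remain. If control weight proves flat, the labels will barely change.

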## Abstract

**Background:**

Weight loss induced only by exercise is frequently less than expected, possibly because of compensatory changes in energy intake and/or energy expenditure. The purpose of the Examination of Mechanisms (E-MECHANIC) of Exercise-Induced Weight Compensation trial is to examine whether increased energy intake and/or reduced spontaneous activity or energy expenditure (outside of structured exercise) account for the less than expected, exercise-associated weight loss.

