An important limitation of the extant literature is the overall short duration of the exercise interventions and the general lack of accuracy of measurements of energy balance (that is, energy intake and energy expenditure) [10]. Further, US national guidelines and recommendations cite specific physical activity goals for health improvement, but this advice is not informed by rigorous research results and does not acknowledge the potential for counterproductive compensatory mechanisms. The Examination of Mechanisms (E-MECHANIC) of Exercise-Induced Weight Compensation trial will directly address these issues. The aim of the E-MECHANIC trial is to test two doses of exercise and their effect on change in all aspects of energy balance, including energy intake, metabolism, physical activity and body composition, using the most precise assessment methods available. The E-MECHANIC investigators hope to effectively determine the source, or sources, of alterations in energy balance that reduce the magnitude of weight loss during an exercise program. In addition, the study researchers intend to determine the behavioral phenotypes associated with participants who do (noncompensators) and those who do not (compensators) lose the expected amount of weight in response to an increase in energy expenditure through exercise.

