### Study design and objectives

The E-MECHANIC study is a three-arm, 6-month randomized controlled trial (RCT). The selected exercise doses reflect current recommendations for (1) general health (8 kcal/kg body weight/wk (8 KKW), or approximately 800 to 1,000 kcal/wk) and (2) weight loss (20 KKW, or approximately 2,000 to 2,500 kcal/wk) [14]. A nonexercise control group will also be included in the study.

The primary objectives of the E-MECHANIC trial are (1) to test whether energy intake increases in response to either or both of two doses of exercise (8 KKW vs. 20 KKW), (2) to test whether the discrepancy between observed and expected weight loss (Wt Loss_diff_) differs between the two exercise groups (8 KKW vs. 20 KKW) and between the control and 20-KKW groups and (3) to determine whether change in energy intake mediates Wt Loss_diff_.

The secondary objectives of the trial are (1) to determine whether change in resting metabolic rate (RMR; adjusted for change in body mass index (BMI)) and activity levels (excluding structured exercise) differ across treatment groups; (2) to determine whether change in body composition differs by exercise dose; and (3) to characterize participants who compensate (that is, fail to lose the amount of weight expected) and compare them with those who do not compensate (that is, lose the amount of weight expected or more).

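### The mediation analysis enters energy intake alone and infers mediation from a non-significant or reduced group term, so it cannot apportion the weight-loss shortfall among the mechanisms the trial names

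*Protocol article*

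**What the plan says.** **Purpose.** The protocol article's abstract sets out "to examine whether increased energy intake and/or reduced spontaneous activity or energy expenditure (outside of structured exercise) account for the less than expected" weight loss. Its Background section adds that the investigators "hope to effectively determine the source, or sources, of alterations in energy balance that reduce the magnitude of weight loss during an exercise program". More than one mechanism is therefore in view.

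**Objectives (Study design and objectives).** Primary objective 3 is "to determine whether change in energy intake mediates Wt Loss_diff". RMR and activity appear in secondary objective 1, which asks whether changes in RMR and in "activity levels (excluding structured exercise) differ across treatment groups". That is a comparison of arms, not a mediation question.

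**Analysis (Data analysis).** The mediation paragraph, presented as an initial step, states "we will test whether changes in energy intake mediate or partially mediate the relationship between group assignment (exercise dose", with Wt Loss_diff as outcome. It then gives a causal-steps sequence: group predicts Wt Loss_diff; change in intake predicts Wt Loss_diff; then group is tested with intake in the model. A group term that is no longer significant leads to the conclusion that intake mediated the effect. A group term that is smaller counts as demonstrated partial mediation. No later step is named, and no mediation model contains RMR or activity.

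**Other analyses that use RMR and activity.** Changes are contrasted between arms in the mixed models. Changes in outcomes, including armband activity, are compared between compensators and noncompensators (Activity level; Data analysis).

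**The concern.** The trial names rival explanations for one shortfall and measures them at baseline and week 24 (Table 1). Its only model for attributing the arm difference in Wt Loss_diff holds one of them. Whatever runs through activity or RMR is then left in the group coefficient or, if it correlates with intake change within arms, is partly absorbed into the intake coefficient. The decision rule adds to this, because a non-significant or smaller group term is read as evidence about intake with no estimate of the indirect effect. At stake is the trial's main interpretive statement: how much of the shortfall is eating and how much is reduced expenditure.

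**Working it through.** **1. The plan's own figure.** The effect to be decomposed is the Wt Loss_diff contrast in Table 3: 60 per arm, difference 2.0 kg, SD 3.3, two-sided α = 0.05.

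- Standard error: 3.3 × √(2/60) = 0.6025.
- Power: Φ(2.0/0.6025 − 1.96) = Φ(1.36) = 0.913; noncentral t gives 0.909. The stated 0.90 reproduces.
- No power or precision is stated for the mediation analysis.

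**2. What the intake-only model reports.** Let M1 be the rise in intake and M2 the fall in non-exercise expenditure (kcal/day). Using the protocol's 7,700 kcal/kg over 24 × 7 = 168 days:

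- Y = b(M1 + M2) + noise, with b = 168/7,700.
- 2.0 kg corresponds to 2.0 × 7,700/168 = 91.7 kcal/day.

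Assumptions not in the documents: the effect splits equally (1.0 kg each); within-arm SDs are 200 for M1 and 100 for M2; r is their within-arm correlation. With M2 omitted, the slope on M1 becomes b(1 + r × 100/200). Hence:

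- Reported intake effect = 1.0 × (1 + 0.5r) kg.
- Residual group effect = 2.0 − 1.0 × (1 + 0.5r) = 1.0 − 0.5r kg.

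| r | Intake effect (true 1.0 kg) | Residual group effect |
|---|---|---|
| −0.3 | 0.85 | 1.15 |
| 0 | 1.00 | 1.00 |
| 0.3 | 1.15 | 0.85 |
| 0.5 | 1.25 | 0.75 |

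If the whole 2.0 kg came from lower expenditure and intake did not shift, the residual group effect would be 2.0 kg with no mechanism attached.

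**3. What the stated rule concludes.** The rule was simulated with 4,000 trials per scenario, 60 per arm, total effect 2.0 kg and SD 3.3. The assumed standardised group shift is 0.63 (200/316, the DLW row of Table 3) in intake, and the same in activity. Step two was read as a regression on intake change alone.

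| True share through activity | r | Full mediation by intake declared | Partial declared |
|---|---|---|---|
| Half | 0 / 0.3 / 0.5 | 49% / 62% / 70% | 43% / 29% / 21% |
| Three quarters | 0 / 0.3 / 0.5 | 23% / 47% / 59% | 63% / 44% / 32% |
| All, no intake shift | 0 / 0.3 / 0.5 | 0.1% / 1.0% / 0.6% | 3% / 42% / 48% |

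**4. Separating the two causes.** In the half-and-half case at r = 0 the intake share is estimated without material bias (median proportion 0.48), yet full mediation is declared in 49% of trials. That part comes from reading non-significance as absence of any other path. The rise to 70% comes from the correlation with the omitted mechanism. In the last row, partial mediation is declared in 42% to 48% of trials at r = 0.3 to 0.5, although intake carries none of the effect, because any reduction counts. The steps written out in the section do not include a check that group predicts intake change; applying one would lower those figures.

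**The case against.** **The analysis matches primary objective 3, which names intake only.** True, and the intake model should stay. But the article also sets itself a wider question, and no listed model apportions the answer.

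**A condensed article calls this an initial step, and later steps may sit in an analysis plan not shown.** Also true: that intake is the sole mediator is established only for this article. But the article does not stop at announcing a first step. It fixes the conclusions to be drawn there, and those can be judged as written.

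**A reader might infer that the plan cannot say anything about activity or RMR, or that nothing else links them to the shortfall.** The documents do not support that. Compensator status is Wt Loss_diff split at zero, and changes in outcomes are to be compared by that status, alongside the between-arm contrasts. What is missing is the share, not all evidence.

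**A reader might infer that intake is always over-credited, or that activity compensation will be reported as a direct effect of exercise.** Neither follows. The first depends on the sign of a correlation the documents do not give; at r = 0 there is no bias, and at negative r intake is under-credited. The term direct effect does not occur in the article, and a finding of partial mediation leaves room for other mechanisms.

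**The illustration is idealised.** It assumes additive mechanisms and error-free mediators and uses the 7,700 kcal/kg conversion. The article itself says that this formula overestimates weight loss, and it also specifies a dynamic model. The illustration shows direction and order of size, not a forecast. Armband error would also weaken the activity path in any joint model.

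**Conclusion.** The point holds in a limited form. The mediation analysis as written cannot apportion the arm difference in Wt Loss_diff among intake, RMR and activity, and its rule lets a non-significant or smaller group term stand as a finding about intake. Under the assumed equal split and SDs, a true 1.0 kg intake share is reported as 0.85 to 1.25 kg for r from −0.3 to 0.5. With half the effect through activity, the rule declares full mediation by intake in 49% to 70% of simulated trials for r from 0 to 0.5.

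That 49% to 70% should not be put down to the omitted mediators alone; it owes much to the significance rule. The correlations, the SDs in the kilogram illustration and the shift in activity are assumptions. The plan should be changed, but the trial's data collection and primary objective 3 are not undermined.

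**What to change.** In the mediation paragraph of Data analysis:

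1. Keep the intake-only model as the analysis for primary objective 3. Report its indirect effect with a bootstrap 95% CI, and drop the inference of full or partial mediation from a non-significant or reduced group term.
2. Add a supporting parallel-mediator model with change in intake, change in adjusted RMR and change in non-exercise activity entered together. Report each indirect effect in kg with its bootstrap 95% CI, and label the remaining group effect *unexplained*.
3. Name the armband, with structured sessions excluded, as the source of activity. Activity derived from doubly labeled water would share error with intake derived from the same measurement.

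**Cost.** Analysis wording and one more model to report; no new data. Intervals will be wider than in the intake-only model, and armband error will attenuate the activity path. A small activity effect should therefore be read with that limit stated.

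### The mediation rule for primary objective 3 can declare mediation where none exists and can overstate its degree

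*Protocol article*

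**What the plan says.** Study design and objectives lists the mediation question as the third primary objective: "to determine whether change in energy intake mediates Wt Loss_diff". The mediator paragraph of Data analysis cites the Baron and Kenny method, calls the work an initial step, and then sets out its own sequence:

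1. Total effect: "determine whether Wt Loss_diff_ is predicted by group, with grouping variables coded as 8 KKW vs. 20 KKW and control vs. 20 KKW".
2. Intake to outcome: "Subsequently, we will test whether change in energy intake predicts Wt Loss_diff". Adjustment for group is not mentioned.
3. Gate and adjusted test: "Assuming that the results are significant, we will then determine whether group significantly predicts Wt Loss_diff_ independently of energy intake".
4. Reading of a non-significant adjusted group effect: "If group does not independently predict Wt Loss_diff_, then the relationship between group and Wt Loss_diff_ may be attributable to change in energy intake", followed by the firmer statement "we will then conclude that change in energy intake mediated the relationship between group and Wt Loss_diff".
5. Reading of a smaller adjusted effect: "If the relationship between group and Wt Loss_diff_ is reduced after accounting for change in energy intake, then partial mediation will have been demonstrated".

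The effect of group on intake is tested elsewhere, under primary objective 1 and through the pairwise contrasts in Data analysis. Nothing in the mediation sequence refers to that result.

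**The concern.** A mediated effect is the product of two paths: group changes intake, and intake changes the outcome among people in the same group. The sequence does not require the first path and does not say that the second is estimated within group. It then draws two conclusions that its tests cannot carry:

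- A p-value of 0.05 or more for the adjusted group effect is read as mediation. That treats failure to detect a direct effect as evidence that there is none.
- Any numerical shrinkage of the group coefficient is read as partial mediation. An adjusted coefficient will often shrink by chance.

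Mediation is the trial's main mechanistic question. Followed literally, the rule could report that intake explains part of the missing weight loss when exercise did not alter intake. It could also report intake as the explanation when most of the effect runs by another route.

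**Working it through.** **Inputs from the article.** 60 completers per arm (Statistical power and sample size). Weight-loss discrepancy: difference 2.0 kg, SD 3.3. Energy intake by doubly labeled water: difference 200 kcal, SD 316 (both Table 3). Two-sided alpha 0.05.

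**Assumption.** The within-arm correlation r between change in intake and the discrepancy is not in the article. It is varied from 0 to 0.7, signed so that an intake rise caused by exercise would add to the group effect.

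**The plan's own power first.** Power ≈ Φ(d·√(n/2) − 1.96), with √(60/2) = 5.477.

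- Discrepancy: d = 2.0/3.3 = 0.606; 0.606 × 5.477 = 3.32; Φ(1.36) = 0.91 (stated 0.90).
- Intake by doubly labeled water: d = 200/316 = 0.633; 0.633 × 5.477 = 3.47; Φ(1.51) = 0.93 (stated 0.93).

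Both reproduce, so these inputs are a fair basis. The article states no error rate for the mediation rule.

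**Why shrinkage is weak evidence.** In least squares on the same participants, total minus adjusted group effect equals â × b̂. Here â is the estimated group effect on intake and b̂ the intake slope adjusted for group. If the true group effect on intake is zero, â falls on either side of zero equally often, so the adjusted effect shrinks in about half of trials. At r = 0.5 about 91% of trials pass both gates, and 0.91/2 ≈ 0.45. The simulated figure is slightly higher because passing the total-effect gate favours trials in which â happened to add to the effect.

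**Simulation.** One two-arm contrast and one intake measure, least squares, 8,000 trials per scenario, step 2 unadjusted for group. The comparator (joint significance) requires both group-to-intake and group-adjusted intake-to-outcome to be significant.

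*No effect of group on intake, true total effect 2.0 kg*

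| r | Full or partial declared | Full only | Joint significance |
|---|---|---|---|
| 0 | 3.5% | 0.1% | 0.2% |
| 0.2 | 31% | 0.8% | 3.1% |
| 0.3 | 45% | 0.8% | 4.7% |
| 0.5 | 48% | 0.6% | 5.2% |
| 0.7 | 50% | 0.1% | 5.0% |

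With a total effect of 1.5 kg the first column runs from 2.6% to 45%, and with 1.0 kg from 1.4% to 30%. False full mediation reaches at most 4.8% (1.0 kg, r = 0.5). Adding a significant group-to-intake test to the written rule cuts the 2.0 kg column to 0.3%–2.7%.

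*Group raises intake by 200 kcal, intake has no effect on the outcome, total effect 2.0 kg.* The rule declares mediation in 15% of trials, against 4.5% for joint significance. Adding the group-to-intake test leaves it at 15%. Adjusting step 2 for group lowers it to 2%–3%.

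*Mediation truly partial, 200 kcal, total effect 2.0 kg.* Mediated part = 200 × r × 3.3/316.

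- r = 0.3: 0.63 kg, 31% of 2.0 kg. The rule concludes unqualified mediation in 31% of trials, although 69% of the effect is direct.
- r = 0.5: 1.04 kg, 52% of 2.0 kg. The rule concludes unqualified mediation in 49% of trials, although 48% of the effect is direct.

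Repeat runs agreed within one to two percentage points.

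**The case against.** **Group-to-intake is tested and may be implied.** Objective 1 tests it, the article gives 0.93 power for it with doubly labeled water, and a named method is cited. If exercise did not change intake, a mediation claim would usually stand beside a null primary result. This is fair: the path is not absent from the trial. What is absent is any statement that the mediation conclusion depends on it. Linking the two would repair the first scenario but not the 15% in the second, nor the overstatement in the third.

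**The text calls this an initial step, and an article is condensed.** True, but the article does not leave the decision rule open. It says what will be concluded and what will count as demonstrated.

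**The correlation is assumed.** True. At zero the false rate is low, so a reader might infer that the rule always, or in half of trials, finds mediation where there is none. The documents do not support that; the supportable statement is a range. Even so, 0.2 already gives about 31%, and a zero correlation sits poorly with the article's own energy-balance premise.

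**The two criteria fail differently.** A reader might infer that the non-significance criterion produces the 50%. It does not: at the planned effect, false full mediation stays below 1%. The shrinkage criterion produces nearly all the false declarations. The non-significance criterion mainly turns partial mediation into unqualified mediation.

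**The 15% scenario rests on one reading.** It requires step 2 to be fitted without group, which the text neither says nor excludes, and an intake change with no bearing on weight. It shows why the adjustment should be stated and is not the main evidence.

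**Conclusion.** The concern holds in a bounded form. The written rule for a primary objective can declare mediation when exercise does not change intake: about 3.5% to 50% of trials at the planned 2.0 kg effect as the assumed correlation runs from 0 to 0.7, almost always as partial mediation. It can also overstate the degree, concluding unqualified mediation in about 31% or 49% of trials when intake carries about a third or a half of the effect. These figures rest on the article's sample size, differences and SDs, on the assumed correlation, and on a single two-arm contrast with one intake measure. The randomised comparisons of intake and of the weight-loss discrepancy, and the power calculations for them, are unaffected.

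**What to change.** For each contrast (8 vs 20 KKW, control vs 20 KKW):

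- Estimate the indirect effect as the group effect on change in intake multiplied by the effect of change in intake on the discrepancy, the latter adjusted for group.
- Give a 95% confidence interval, for example by bootstrap, and claim mediation only if it excludes zero.
- Report the direct effect and the proportion mediated, each with a confidence interval, so that degree is shown rather than inferred from a p-value.
- Delete the criteria that read non-significance as mediation and shrinkage as partial mediation.

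The choice of covariates, and whether to keep the significant-total-effect gate, can stay with the sponsor; neither is an error in the document.

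The cost is revised wording, a small amount of code and a somewhat stricter criterion, with no new data. The loss in sensitivity looks small: in the partial-mediation scenarios above, joint significance of both paths (a stand-in for the interval) detected mediation in 86% and 93% of trials, against 90% and 91% declared by the current rule.
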